#### Sample size estimation

Power Analysis and Sample Size Software version 15.0 (PASS, NCSS Statistical Software, Kaysville, UT, USA) was used to determine the study’s sample size. An alpha of 0.05 and a power of 0.9 are used in the study. Based on preliminary trial results, the Clancy Autism Behavioral Scale (CABS) score indicates a curative effect, so the mean and standard deviation of the paired differences are 5 and 8, respectively (15). The PASS software calculation resulted in a minimum requirement of 34 participants per group, accounting for an estimated 20% dropout rate. Considering a 15% rate of invalid MRI data based on previous experience, a minimum of 40 subjects will be recruited per group. Therefore, 40 patients will be enrolled in each group, totaling 80 patients for the study.

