### Statistical analysis

Basic analyses will be conducted using SPSS 25.0 software. At baseline, independent samples t-tests will be used to determine if there is no statistical difference between the two intervention groups; paired samples t-tests will then be used to examine the differences between mean scores before and after the taVNS intervention to determine the effectiveness of the treatment. Additionally, for the imaging study, we will use two-sample t-tests to compare brain network parameters between the HC and sham groups, as well as paired-sample t-tests to determine brain network parameters between the sham and active groups. Based on age and gender as covariates, a two-sample t-test will be used to compare the small-world properties and global parameters of the anatomical network between the HC group and the sham group. The level of significance for all statistical tests is set at p< 0.05. A Bonferroni correction will be performed on the t-tests utilized to examine group differences in behavioral and brain measurements, to account for multiple comparisons.

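### The sample size is a one-group before-after calculation, so the only stated power (0.9) does not apply to the active-versus-sham comparison, where the same inputs give about 69%

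*Protocol article*

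**What the plan says.** The Sample size estimation section of the protocol article sets the error rates: "An alpha of 0.05 and a power of 0.9 are used in the study". The inputs are on the Clancy Autism Behavioral Scale (CABS) and are credited to preliminary results: "the mean and standard deviation of the paired differences are 5 and 8, respectively (15". The result is given per arm: "The PASS software calculation resulted in a minimum requirement of 34 participants per group, accounting for an estimated 20% dropout rate". A further allowance follows: "Considering a 15% rate of invalid MRI data based on previous experience, a minimum of 40 subjects will be recruited per group". The section ends with "40 patients will be enrolled in each group, totaling 80 patients for the study".

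The Study design section describes randomisation to active or sham taVNS under double blinding. The Statistical analysis section judges effectiveness by paired t-tests on mean scores before and after the intervention. For the clinical scales, the only comparison of the two intervention groups that it describes specifically is the baseline check. On the significance level it says "The level of significance for all statistical tests is set at p< 0.05", without stating whether tests are one- or two-sided.

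**The concern.** A mean and SD of paired differences answer one question: does a single group change from baseline? A sham-controlled trial asks whether the active arm changes more than the sham arm. Two things differ:

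- **Variance.** The difference between two independent mean changes has twice the variance of one mean change, for the same number per arm.
- **Effect.** A pre-post change of 5 equals the active-minus-sham difference only if sham children do not change on average. CABS is parent-reported, and the sham is designed to feel like real stimulation, so zero change under sham is a strong assumption. The article does not state it.

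At stake is how a non-significant active-versus-sham result would be read. The article gives no other power figure, so a reader is likely to weigh such a result against 90%, although the design does not provide that for this comparison.

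**Working it through.** **Inputs from the article:** alpha 0.05; power 0.9; mean paired difference 5; SD of paired differences 8; dropout 20%; invalid MRI 15%; 40 enrolled per arm.

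**Assumed or derived:** a two-sided test (not stated); 40 × 0.8 = 32 completers per arm; for the between-arm check, SD of change 8 in both arms.

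**1. Reproducing the plan's figures.** One-group paired formula, normal approximation:

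n = (1.960 + 1.282)² × (8/5)² = 26.9, rounded up to 27

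- With 20% dropout: 27/0.8 = 33.75, rounded up to 34, as stated.
- With 15% invalid MRI: 34/0.85 = 40.0, as stated.

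Other formulas with the same inputs do not give 34:

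| Calculation | Evaluable per group (z / t) | With 20% dropout (z / t) |
|---|---|---|
| One-group paired, two-sided | 27 / 29 | **34** / 37 |
| One-group paired, one-sided | 22 / 24 | 28 / 30 |
| Two-sample, two-sided | 54 / 55 | 68 / 69 |
| Two-sample, one-sided | 44 / 45 | 55 / 57 |

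Only the two-sided paired normal approximation matches. The step from 34 to 40 would follow from any formula that gave 34, so it is not separate evidence.

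**2. Power for the within-arm test.** A paired t-test with 32 completers, mean change 5 and SD 8 has 92.8% power. The size is adequate for that test.

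**3. Power for active versus sham.** Two-sample t-test on change, two-sided 0.05, noncentral t with 2n − 2 degrees of freedom and noncentrality δ / (8 × √(2/n)). For n = 32 and δ = 5, the standard error is 8 × √(2/32) = 2.0 and the noncentrality is 2.5.

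| Per arm | Active-minus-sham difference | Power |
|---|---|---|
| 40 (no loss) | 5 | 78.8% |
| 32 | 5 | 69.2% |
| 32 | 4 (sham improves by 1) | 50.4% |
| 32 | 3 (sham improves by 2) | 31.5% (0.3148) |

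The normal approximation gives 70.5% at 32 per arm and 79.8% at 40, so the choice of formula matters little.

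**4. What 90% or 80% would take.** For a difference of 5, power is 89.6% at 54 per arm and 90.1% at 55, so 55 evaluable are needed. Enrolment is then 55/0.8 = 68.75, or 69 per arm. With 32 per arm, 80% power is reached at a difference of 5.7 points (80.1%).

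**The case against.** The strongest defence is that the calculation fits the test the article plans. The inputs are labelled as paired differences, the efficacy test is a paired before-after t-test, and that test has 92.8% power at 32 completers. This stands: the arithmetic contains no error. It does not rescue the power statement for the randomised question, because that test makes no use of the sham arm.

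A reader might infer that the article claims 90% power for active versus sham. It does not say so; it says only that this power is used in the study. The point is that the sole power figure in a sham-controlled trial belongs to a different comparison.

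A reader might also take the 15% invalid MRI off again, reaching 40 × 0.8 × 0.85 = 27 per arm and about 62% power. That does not hold for CABS, which is a parent-reported questionnaire; an unusable scan does not remove its score. The relevant number is 32.

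Baseline adjustment could recover some power. With an assumed baseline to follow-up correlation of 0.5 to 0.7, the residual SD is 8 × √((1 + ρ)/2) = 6.93 to 7.38, and power at 32 per arm is about 81% to 76%. This is illustration only: the article gives no correlation and plans no adjusted analysis of the clinical scales, and the result is still below 90%.

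Finally, the Bonferroni sentence mentions group differences in behavioural measures, so some between-arm testing may be intended. It names neither an outcome nor a time point, and the sample size is not tied to it. A separate analysis plan might define such a test, but it would not change what 34 and 40 were calculated for.

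**Conclusion.** The point holds in this form. The 34 and 40 per group come from a one-group paired calculation, so the stated 0.9 is the power to detect change from baseline within an arm. For active versus sham, the same inputs give about 69% with 32 completers per arm and 79% if nobody is lost. At 32 completers, the chance of missing a true 5-point difference is about 31%, against the 10% that the stated power suggests.

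This rests on a two-sided 0.05 test, an SD of change of 8 in both arms, and 5 points as the full active-minus-sham difference. The last assumption favours the plan: an improvement of 1 or 2 points under sham lowers power to about 50% or 31%. The one-group origin is inferred, since the article prints neither the intermediate 27 nor the formula. The inference is strong, because the inputs are called paired differences and no two-sample variant comes near 34.

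**What to change.** Keep the 80 patients and change two sections together.

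- **Statistical analysis:** name the between-arm comparison of CABS change as the efficacy test. Without this, the restated power would refer to a test that the trial does not plan.
- **Sample size estimation:** replace the 90% power statement with wording such as: *40 per arm gives about 32 completers per arm after 20% dropout; for the active-minus-sham difference in CABS change (assumed SD 8, two-sided 0.05) this gives about 69% power for 5 points and 80% for 5.7 points.* Add that 5 points is assumed as the active-minus-sham difference.

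Leave baseline-adjusted power figures out unless the Statistical analysis section is changed to plan that analysis, with its correlation assumption stated.

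The cost is a change of text and of the named efficacy test, with no added patients. The downside is a less favourable stated power. If the sponsor wants 90% for 5 points, the alternative is about 69 enrolled per arm, 138 in all, instead of 80.

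### The minimum of 34 per group is a normal-formula figure; the planned paired t-test needs 29 completers (37 enrolled) for 0.9 power, which the 40 enrolled already exceed for CABS

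*Protocol article*

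**What the plan says.** Under Sample size estimation, the protocol article fixes the error rates: "An alpha of 0.05 and a power of 0.9 are used in the study". It does not say whether alpha is one- or two-sided. The effect is taken from preliminary results on CABS: "the mean and standard deviation of the paired differences are 5 and 8, respectively". From these inputs it reports: "The PASS software calculation resulted in a minimum requirement of 34 participants per group, accounting for an estimated 20% dropout rate". It then adds an allowance for imaging, "Considering a 15% rate of invalid MRI data based on previous experience, a minimum of 40 subjects will be recruited per group", and ends with 40 per group and 80 in total. PASS 15.0 is named as the software, but not the procedure used within it, so the reader cannot tell whether the SD was treated as known or estimated.

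Under Statistical analysis, the test of treatment effect on the scales is named: "paired samples t-tests will then be used to examine the differences between mean scores before and after the taVNS intervention". The same section sets significance at 0.05 and announces a Bonferroni correction for t-tests of group differences in behavioural and brain measures.

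Under CABS, the scale is described as parent-reported.

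**The concern.** A figure presented as the minimum for 0.9 power should give 0.9 power when the planned test is run on the printed inputs. With 34 enrolled and 20% lost, about 27 children per group remain. For a paired t-test with a standardised change of 5/8 = 0.625, 27 falls slightly short.

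This paragraph is the article's only stated power justification, and the 40 is built on the 34. A colleague who re-runs the calculation for the planned test will not obtain the printed minimum, and the paragraph does not say what 40 delivers for CABS or for imaging. Whether a within-group change is a suitable basis for sizing a sham-controlled trial is a separate question and is not argued here.

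**Working it through.** **Inputs.** From Sample size estimation: mean paired difference 5, SD 8, alpha 0.05, power 0.9, dropout 20%, invalid MRI 15%, enrolment 40 per group. From Statistical analysis: paired t-test. Assumed: two-sided alpha.

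**Step 1: reproduce the printed figures.** The normal formula with a known SD is n = [(z₀.₉₇₅ + z₀.₉₀) × SD / mean]².

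- n = [(1.960 + 1.282) × 8/5]² = 26.9, so 27 completers.
- Dropout: 27/0.8 = 33.75, so 34.
- Invalid MRI: 34/0.85 = 40.

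All printed figures are matched, and both inflation steps are done correctly. The other variants tried do not give 34:

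| Calculation | Completers | Enrolled at 20% dropout |
|---|---|---|
| Normal, two-sided | 27 | 34 |
| Paired t, two-sided | 29 | 37 |
| Normal, one-sided | 22 | 28 |
| Paired t, one-sided | 24 | 30 |

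Multiplying the two-sided t result by 1.2 instead of dividing by 0.8 gives 29 × 1.2 = 34.8, so 35, which also does not match.

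**Step 2: power of the planned test.** For the two-sided paired t-test, power is the probability that a noncentral t variable, with n − 1 degrees of freedom and noncentrality 0.625 × √n, falls beyond the critical value t₀.₉₇₅ in either direction.

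| Completers | Noncentrality | Power, paired t | Power, normal formula |
|---|---|---|---|
| 27 | 3.248 | 0.878 | 0.901 |
| 28 | 3.307 | 0.890 | 0.911 |
| 29 | 3.366 | 0.901 | 0.920 |
| 32 | 3.536 | 0.928 | 0.942 |

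The smallest number that reaches 0.9 with the t-test is 29. With 20% dropout, 29/0.8 = 36.25, so 37 enrolled. The printed 34 is 3 lower. At 27 completers the shortfall is 0.900 − 0.878 = 0.022.

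**Step 3: what 40 enrolled give.**

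- CABS: 40 × 0.8 = 32 completers, power 0.928 at unadjusted alpha 0.05. This is above 0.9, and 40 is above 37.
- Completed course and valid MRI: 40 × 0.8 × 0.85 = 27.2, so about 27 per group. No power follows from this number, because the article gives no effect size for any network measure.

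**The case against.** **The printed figures follow from a recognised formula.** This is correct, and the article does not say that a t calculation was used. The 34 is neither unexplained nor a slip in the dropout arithmetic. But the test it is meant to size is a t-test, and for that test 34 is not the minimum.

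**The gap is within the rounding of the inputs.** Mean and SD are printed as whole numbers. With SD 7.8 in place of 8, 27 completers would give 0.894. This limits the importance of the point. It does not make the printed minimum follow from the printed inputs.

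**Sidedness is not stated.** With one-sided alpha, 27 completers would give 0.935. That reading does not rescue the figure, because the one-sided minimum would be 30 enrolled (t) or 28 (normal). Two-sided is the only reading tried that yields 34.

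**Nothing changes in practice.** The 34 is an intermediate figure, and 40 are enrolled. This stands, and it is why the point is minor.

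**A stronger reading that the documents do not support.** A reader might infer that 40 is also too few because it does not cover dropout and invalid MRI together. The powered outcome is CABS, which parents report, so an unusable scan does not remove a CABS score. On the plan's own base of 27, 27.2 children remain after both losses, so its chain is internally consistent. The article claims 0.9 power for no MRI outcome, and carrying the CABS effect over to network measures would be a construction of the reader's.

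**Conclusion.** The printed minimum is wrong as written for the planned test, by a small amount. It should be 29 completers, or 37 enrolled, per group instead of 27 and 34. The stated 0.9 power is 0.878 at the stated minimum, 2.2 percentage points lower.

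This rests on the article's mean of 5 and SD of 8 taken at face value, 20% dropout applied by division as the article does, and two-sided alpha of 0.05, which is an assumption.

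The trial as enrolled is not underpowered for the paired CABS change: about 32 completers give about 0.93. That holds at unadjusted alpha. The wording on Bonferroni does not make clear whether the paired tests are included. If they are, and alpha is divided by, say, four, power at 32 completers would be about 0.80. The divisor of four is illustrative and not stated in the article. Severity is minor.

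**What to change.** Restate the sample-size paragraph along these lines, leaving enrolment as it is:

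- With a mean paired CABS change of 5, SD 8 and two-sided alpha of 0.05, a paired t-test needs 29 completers per group for 0.9 power, or 37 enrolled with 20% dropout.
- Enrolling 40 per group is expected to leave about 32 with CABS data and gives about 0.93 power for the paired CABS change, before any Bonferroni correction.
- About 27 per group are expected to have both a completed course and valid MRI. No power is claimed for MRI outcomes, because no effect size is available for them.

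If a one-sided alpha was intended, the authors should say so and recompute, since 34 does not follow from that either.

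The cost is a few sentences. No patients are added, and neither treatment nor analysis changes. The only loss is that the stated minimum looks slightly less favourable.

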Based on the aforementioned evidence, we designed our protocol with two primary objectives: First, it aims to examine the therapeutic effects of taVNS in individuals diagnosed with HFA; Second, it intends to investigate the process of brain network remodeling after taVNS using functional imaging techniques. We will use graph-theoretic analysis to compare the brain network characteristics of individuals with HFA before and after receiving taVNS. Additionally, we will examine the differences in these characteristics between patients with HFA and healthy controls, considering both structural and functional connectivity perspectives. Our hypothesis posits that taVNS has the potential to enhance the efficiency and flexibility of brain networks in HFA patients, leading to an improvement in their social cognitive abilities.

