#### Network analysis

The small-world properties, global properties, and local properties of brain networks will be analyzed using graph theory. There are five small-world properties: clustering coefficient (Cp), characteristic path length (Lp), normalized clustering coefficient (Gamma, γ), normalized characteristic path length (Lambda, λ), and small-worldness (Sigma, σ) (50, 51). A network is regarded to have small-world features when γ >> 1, λ ≈1, and σ > 1 (48, 52). Global network properties consist of global efficiency (Eg) and local efficiency (Eloc). Nodal properties, or local properties, include nodal efficiency (NE), betweenness centrality (BC), and nodal degree centrality (DC) (51, 53). A node’s NE can be measured as its capacity to transmit information to other nodes, its BC as its capacity to influence the flow of information between all other nodes, and its DC can be measured as the number of edges it connects with (52, 54).. In a previous publication, these network measures were defined in detail (54).

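### The stated power of 0.9 rests on CABS alone, with the MRI allowance added on top, so it is not shown for the network objective that the plan also calls primary

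*Protocol article*

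**What the plan says.** The Introduction states: "we designed our protocol with two primary objectives". The first is the therapeutic effect. On the other it says: "Second, it intends to investigate the process of brain network remodeling after taVNS using functional imaging techniques". The method named there is to "compare the brain network characteristics of individuals with HFA before and after receiving taVNS", together with a comparison of patients with healthy controls.

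Under Sample size estimation the protocol says: "An alpha of 0.05 and a power of 0.9 are used in the study". The only effect given is for CABS: "the mean and standard deviation of the paired differences are 5 and 8, respectively". The calculation "resulted in a minimum requirement of 34 participants per group, accounting for an estimated 20% dropout rate", and the next step is "Considering a 15% rate of invalid MRI data based on previous experience, a minimum of 40 subjects will be recruited per group". No network metric, effect size or SD appears in that section.

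Network analysis lists five small-world measures, two global efficiency measures and three nodal measures, and the plan builds both a functional and a structural network. Statistical analysis compares network parameters between sham and active and between healthy controls and sham. It prescribes a Bonferroni correction for behavioural and brain tests without saying how many tests it covers.

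**The concern.** An objective called primary would normally be covered by the stated power, or the plan would say that it is not. Here the power is attributed to the study as a whole, while its only input is a parent-reported questionnaire. The MRI allowance makes the final 40 per group look as if imaging had been sized. In fact it only brings the number of usable scans back to the number that the CABS calculation produced.

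What is at stake is how a null network result will be read. A reader who credits the imaging comparison with 90% power may take a null result as evidence against remodelling. At this sample size it may say little about differences below roughly 0.8 to 0.9 SD between arms, or below about 1 SD once several metrics share the alpha.

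**Working it through.** **Inputs from the protocol (Sample size estimation).** Alpha 0.05; power 0.9; CABS paired difference 5, SD 8 (ratio 5/8 = 0.625); dropout 20%; invalid MRI 15%; 40 per group. Sidedness is not stated, but a two-sided test reproduces the figures.

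**Step 1: reproduce the plan's own chain.**
- Paired normal formula: n = ((1.960 + 1.282) x 8/5)^2 = 26.9, so 27.
- Dropout: 27/0.80 = 33.75, so 34.
- Invalid MRI: 34/0.85 = 40.

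The chain reproduces exactly. The 40 is therefore the CABS number for a one-group paired change, inflated twice.

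**Step 2: children with usable imaging.** Undoing both losses gives 40 x 0.80 x 0.85 = 27.2, about 27 per arm. This takes 15% as a loss per child. If 15% applied independently to each of two scans, the number of complete pairs would be 40 x 0.80 x 0.85 x 0.85 = 23.1, about 23. The protocol does not say which is meant.

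**Step 3: detectable differences.** In the normal approximation, the detectable difference is (z for 1 - alpha/2 + z for power) x sqrt(2/n) between arms, and the same sum divided by sqrt(n) for a paired change. With n = 27 and 90% power, (1.960 + 1.282) x sqrt(2/27) = 0.88 SD between arms, and 3.242/sqrt(27) = 0.62 SD paired. The noncentral t, used below, is slightly less favourable.

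| Comparison | n | Tests sharing alpha 0.05 | 90% power | 80% power |
|---|---|---|---|---|
| Active vs sham | 27 per arm | 1 | 0.90 SD | 0.78 SD |
| Active vs sham | 23 per arm | 1 | 0.98 SD | 0.84 SD |
| Active vs sham | 27 per arm | 7 (assumed) | 1.12 SD | 1.00 SD |
| Pre-post within one arm | 27 | 1 | 0.65 SD of the change | 0.56 SD of the change |
| Pre-post within one arm | 27 | 7 (assumed) | 0.82 SD of the change | 0.73 SD of the change |

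The family of seven is the five small-world plus the two global measures in one network type. The between-arm figures take no credit for baseline adjustment.

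**Step 4: power at the planning ratio.** The ratio 0.625 belongs to CABS. It serves here only as a yardstick, because no network effect is given. With n = 27:
- Active vs sham: 62% for one test, 32% over seven.
- Pre-post within one arm: 88% for one test, 63% over seven.

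**Step 5: effect of the allowance on CABS.** Without it, 34 x 0.80 = 27.2, about 27 children, give CABS data. With it, 40 x 0.80 = 32 do. Paired t-test power at 0.625 rises from 0.88 to 0.93.

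**The case against.** Five points can be made for the plan.

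- The sentence after the power statement names CABS as its basis, so the document does not expressly claim 0.9 for imaging. This stands, and it is why the point is that the power is not shown for that objective, not that a false figure is given. It does not remove the mismatch with an objective called primary.
- Elsewhere the network aim reads as lower in rank. The Abstract puts the therapeutic effect first, the Discussion describes the network work as exploring, and the Limitations speak of preliminary insights. This is fair, and it makes the fix easy, but the Introduction still ranks both aims as primary.
- A reader might infer that the imaging can detect only differences of about 0.9 SD. The documents do not support that as a general statement. The figure holds for active vs sham, one unadjusted test, 90% power and 27 per arm. The before-after comparison named in the Introduction has a smaller detectable effect, although a within-arm change does not by itself attribute remodelling to the stimulation.
- A reader might also infer that the MRI allowance does nothing for CABS. That is wrong, because the six extra children per arm add CABS data (Step 5). Keeping enough usable scans is an ordinary reason for such an allowance.
- The Bonferroni family may be fixed in an analysis plan that is not shown. Seven is therefore an assumption, and the absence of a stated family is not itself the criticism.

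**Conclusion.** The point holds with its conditions. The protocol names two primary objectives, and its power of 0.9 is derived for one of them only, as a paired within-group CABS change. The MRI allowance is stacked on that number without any network effect size.

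For the randomised contrast on a single network metric, the trial has 90% power only for differences of about 0.90 SD or more (0.98 SD if 23 per arm are evaluable). Spread over seven metrics, this becomes about 1.12 SD. At the CABS planning ratio, 0.9 is not reached on either reading of the network comparison once the alpha is shared among seven tests.

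This rests on three assumptions: dropout and MRI loss multiply, as in the plan's own sequence; 15% is a per-child loss; and the correction covers seven tests.

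A reader might take the criticism to mean that 0.9 is secure for CABS in every use. It is not, because the calculation is one-group and paired and does not establish 0.9 for CABS between active and sham. This is a point that should be corrected, and wording is enough to do so.

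**What to change.** In Sample size estimation, state that the 0.9 refers to the paired within-group CABS change only, and not to the network objective or to any between-arm comparison. Say whether 15% is a loss per child or per scan. Give the imaging sensitivity with its conditions. For example, with about 27 evaluable children per arm (about 23 if the loss is per scan), one unadjusted two-sided 0.05 active-vs-sham test detects about 0.90 SD at 90% power or 0.78 SD at 80% (0.98 or 0.84 SD with 23).

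In the Introduction, Network analysis and Statistical analysis, rank the network objective below the clinical one. At the least, name one key network endpoint per network type at W12 and label the remaining network metrics exploratory. Global efficiency would fit the hypothesis about efficiency and is already defined. That choice is the investigators', since the hypothesis also mentions flexibility and local efficiency is listed too.

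No extra children or scans are needed. The cost is a less favourable stated figure and a lower rank for the imaging aim.
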